### **Side effects**

Side effects will be continually monitored throughout the study as part of symptom control. (Appendix IV)

| Amitriptyline |
|----------------------|
| Dry mouth            |
| Sedation             |
| Weight gain          |
| Confusion            |
| Dizziness            |
| Palpitations         |
| Constipation         |

|       |
|-------|
| Other |
|-------|

Patients who develop side effects will be assessed by a doctor. Patients assessed as having serious adverse events will be withdrawn from the study, and reasons recorded. The total period of the study will be 6 weeks from enrolment. After being enrolled, subjects will be monitored for pain relief, symptom control and quality of life by the nurse, after which an intervention will be put in place. Monitoring will be done weekly by a professional nurse. Intervention can be one of the following:

- Increase the dose, and continue with the trial
- Maintain the dose, and continue with the trial
- Stop the drug because of adverse events, and drop from the study

For those that have been found to be not effective, alternative treatment will be offered.

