## Study Summary

**Study purpose:** to assess the effectiveness of Amitriptyline compared to placebo in the management of moderate to severe HIV- related peripheral neuropathy in a population using ARV and not using ARV therapy

**Study design:** A double blind randomised controlled trial using a cross over design

**Sample Size:** 124 participants; 62 on ARV therapy and 62 not on ARV therapy followed up for a total of 15 weeks

**Study population:** adult men and women with documented HIV infection and moderate to severe HIV related distal sensory neuropathy

Visit schedule: An information session with recruitment, followed by a screening visit and an enrolment visit. After enrolment there will be five scheduled visits and weekly telephonic follow-up if written consent provided for that. Optional visits to the Palliative care centres may be done at any time during office hours for concerns, advice or further information. After hours telephonic contact will be available.

Study duration: the total duration of the study is 14 months. Three months for start up, training and preparation, enrolment closes after 6 months; the last participant exiting at month 11, and three months analysis and write up.

Primary objective: A measurement of the difference in pain intensity at the beginning and end of each 6 week treatment period.

Secondary objective: These will be adverse side effects of treatment, minimum effective doses, maximal tolerated doses, mood and effect on activities of daily living.

Study sites: Participants will be recruited from the Nthabiseng HIV Clinic at the Chris Hani Baragwanath Hospital, the Helen Joseph Hospital HIV clinic, and the palliative care clinic and outreach services.

Regulatory and monitoring: The Medicines Control Council (MCC) approval is not required since the drug is being used for indicated purposes. The MCC will be notified. The trial will be registered with the SA National Trials Register, and the Cochrane trials register. Ethical approval will be sought from the Wits REC and regular progress reports submitted as well as SAE, AEs and protocol violations. A study DSMB will be constituted who will perform an interim analysis as well as monitor the trial for safety and protocol violations.

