## **Unscheduled visits, withdrawal from study**

Extra visits will be allowed for adverse event. They will be coded thus; if in week 3, V 3.1. Withdrawal from the study shall be immediately effected on request, a form in reasons for withdrawal shall be filled in and another either allowing or withdrawing permission for utilisation of existing data.

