### ***Data collection, management and analysis***

All patients will be allocated a unique identifier that will also serve as their file number on site. All the information for the patient, laboratory results, and questionnaires from different visits, together with the signed informed consent will be kept in the patient's file. The files will be locked up in a cupboard with limited access control.

Double entry of data collected will be entered using Microsoft Access. R statistical package will be used to analyse the data. Descriptive statistics will be used to describe the demographics and clinical characteristics of the population studied.

The primary outcome (pain relief between baseline and end of the study) will be compared for the

- significance of overall pain relief for repeated measures using univariate analysis of variance (ANOVA)
- Association of the drug and the level of pain relief between different subjects using ANOVA.

The number needed to treat (NNT) will be calculated to assess the effectiveness of the drugs, while the number needed to get severe side effects will be calculated as NNF. During analysis subjects will be adjusted according to exposure to neurotoxic drugs. Analysis will also be done using the intention to treat analysis, where all randomised subjects will be included in the analysis to reduce bias.

The number treated analysis will also be done looking only at those subjects who managed to reach the maximum dose of the drugs. This however is subject to selection bias as subjects who developed side effects and those who were lost to follow up will be excluded. The effect of the use of other pain medication in together with the intervention being tested will also be analysed.

The results will be adjusted for ART during analysis, as all patients including those already on ART will be included in the study.

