Placebo-controlled: The ethics of a placebo controlled trial as opposed to head to head comparison may be debated. In the presence of increasing evidence of effective treatments it would be argued that a head to head comparison be used. However there is no evidence of an effective treatment for HIV related DSN. Thus a comparator would be hard to come by. Also in pain trials the placebo effect is well documented, making a conclusion more difficult. Use of other pain relieving medication for other pains or as rescue treatment: Participants will be able to continue to use other pain relieving drugs that they may be having or to access 'rescue' treatment (either mild opiate or NSAID). If amitriptyline is the only feasible option, they will be removed from the study and offered amitriptyline. Use of rescue medication for NP will be allowed and documented, and its impact on the results will be taken in to account in the analysis.

Cross over design is feasible and brings several advantages over a parallel group design. (See above).

Use of inactive placebo in pain trials: Ethical guidance does not recommend use of placebo in pain trials when there proven treatments exists, and where head to head comparisons are recommended. However because of a marked placebo effect in pain studies, the use of placebo where there is little or no evidence for treatment is recommended. The magnitude of this placebo effect is also considered in the sample size calculation. In the case of HIV related DSN there is no proven treatment. There are many negative trials for HIV DSN, including amitriptyline.

Pain during washout period: There will be a three weeks washout period between arm A and arm B. The  $\frac{1}{2}$  life of amitriptyline is 10-50 hours, with an average of 16 hours. It is eliminated over several days, primarily in the urine as active and inactive metabolites.

Choice of amitriptyline: This is a widely available drug, on the South African EDL. The two previous trials for HIV DSN have shown the drug to be well tolerated. There are no documented or theoretical drug interactions with ARV therapy. Whilst two trials have shown no effect, these were tested on a different population, for all levels pain. Achieving a clinical effect for mild levels of pain may have masked any effect for moderate to severe pain. There

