## **DATA COLLECTION MANAGEMENT AND ANALYSIS**

Data will be entered in real time by a data capturer into a Microsoft Access database. 20% of random sample of data will be double entered by a second data enterer and checked for error rate. The double entry will be adjusted according to the error rate. Hard copy of the

consent forms will be kept in a separate locked filing cabinet. Hard copy of the data forms will be kept in another filing cabinet. After closure of the study, forms will be archived and stored for 7 years. Analysis will be in an intention to treat basis. Primary and secondary outcome measures will be calculated and tested for statistical significance by the biostatistician.

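### The removal rules end follow-up as well as study drug, so the promised intention-to-treat analysis of all randomised patients would rest on missing-data assumptions

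*Protocol*

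**What the plan says.** Three rules in the Protocol end participation in the study, not only treatment:

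- Side effects, as one of three options at weekly review: "Stop the drug because of adverse events, and drop from the study". The other two options keep the patient in the trial.
- Side effects, for serious events: "Patients assessed as having serious adverse events will be withdrawn from the study, and reasons recorded". The definitions of a serious event elsewhere in the Protocol go by outcome, such as hospitalisation, and require no link to the drug.
- Ethics review, after allowing patients to keep other analgesics or take rescue treatment: "If amitriptyline is the only feasible option, they will be removed from the study and offered amitriptyline".

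On withdrawal at the patient's request, the section on unscheduled visits and withdrawal provides two forms: one for reasons, and "another either allowing or withdrawing permission for utilisation of existing data". It says nothing about collecting later outcomes.

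The first of the two data and analysis sections promises intention to treat, "where all randomised subjects will be included in the analysis to reduce bias". The later section of nearly the same title says "Analysis will be in an intention to treat basis" and does not mention all randomised patients. The Study Summary gives the primary objective as "A measurement of the difference in pain intensity at the beginning and end of each 6 week treatment period".

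**The concern.** The Protocol treats the end of study drug and the end of follow-up as one event. The reasons for leaving (intolerance, a serious event, pain that only amitriptyline is thought able to relieve) are plausibly linked to the treatment being taken. If outcomes are not collected after these exits, the comparison of randomised treatments depends on what is assumed about the patients who left.

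The Protocol recognises this problem in one place. It says that the analysis restricted to patients reaching the maximum dose is open to selection bias, because patients with side effects and those lost to follow-up drop out of it. It does not carry that remark over to the main analysis, where the removal rules produce the same kind of loss.

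At stake is whether the trial estimates the effect of offering amitriptyline to everyone randomised, or an effect that leans on patients who tolerated the drug and managed on placebo.

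**Working it through.** **1. What a removed patient contributes.** Pain is recorded in a daily diary, at nurse calls, and at visits in weeks 3, 6, 9, 12 and 15. Period 1 ends at week 6, and period 2 runs from week 9 to week 15.

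- Removed before week 6: baseline plus diary, call and any week 3 data up to exit. The week 6 score and all of period 2 are missing, so there is no within-patient contrast.
- Removed in period 2: a complete period 1 and part of period 2. The week 15 score is missing.

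The loss therefore differs by sequence. Intolerance of amitriptyline costs a patient who takes it first everything after exit, including the whole placebo period. It costs a patient who takes it second only the rest of the last period.

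**2. Exit rules against the promised analysis.** The analysis set is all randomised patients, and the outcome is change over each 6-week period. The exit rules remove patients before that outcome is measured, and no section provides for measuring it afterwards.

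**3. Is power the problem?** The sample size section gives 90% power, alpha 0.05, a difference of 2 and a spread read here as SD 2. A two-sided two-sample t calculation gives 22.02 per arm, rounded up to 23, so 2 × 23 = 46, which is the stated figure. Enrolment is 62 per stratum, so the loss that brings a stratum down to 46 is 1 − 46/62 = 25.8%. Taking a cautious SD of 4 for the within-patient difference, paired-t power per stratum is:

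| Loss | Patients left | Power |
|---|---|---|
| 10% | 55 | 95% |
| 20% | 49 | 93% |
| 25.8% | 46 | 91% |
| 30% | 43 | 89% |
| 40% | 37 | 84% |

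Power holds up well. Extra patients do not correct selective loss, so the issue is bias.

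**4. Possible size, by assumption.** The Protocol gives no rate of stopping for adverse events. Its only nearby figure is about 10% overall loss to follow-up, and 0.10 × 124 = 12.4 patients. Let q be the fraction removed, 2.0 the effect in those who complete (the design difference), and d the effect in those removed:

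effect over all randomised = (1 − q) × 2.0 + q × d

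| q | d = 0 | d = −1 | Completers |
|---|---|---|---|
| 10% | 1.8 | 1.7 | 2.0 |
| 20% | 1.6 | 1.4 | 2.0 |
| 30% | 1.4 | 1.1 | 2.0 |

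This covers one route only, patients who cannot tolerate amitriptyline. For patients removed because pain was unrelieved on placebo, d could exceed 2.0. The formula then gives an all-randomised effect above 2.0, and completers would understate it. The documents give no figures to weigh one route against the other.

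**The case against.** Several stronger readings are tempting, and the text does not support them.

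- **Intention to treat is impossible, or removed patients have no outcome.** A reader might infer this, but diary, call and visit scores exist up to exit, and anyone removed in period 2 has a complete period 1. All randomised patients with such data could enter a mixed model or imputation, which a statistical analysis plan not shown here may specify. For the same reason it does not follow that only a completer analysis remains.
- **Every adverse event leads to removal.** It does not. Only events that stop the drug, and serious events, end participation.
- **Uncontrolled pain on placebo leads to removal.** Rescue treatment is allowed, documented and to be considered in the analysis. Removal applies only when amitriptyline is the sole feasible option, and in either arm. That it would fall mainly on placebo is an inference.
- **The bias favours amitriptyline.** Losing intolerant patients would tend to flatter the drug, and losing patients with unrelieved placebo pain would tend to flatter placebo. The Protocol also describes the drug as well tolerated.

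A further objection is that missing data belong in the analysis plan. That is true of how they are handled. Whether outcomes are collected after drug is stopped is a matter of trial conduct, which the protocol fixes, and no analysis plan can recover scores never taken.

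It is also fair to say that follow-up alone does not solve everything in a crossover. A patient given open amitriptyline during the placebo period would contribute active-drug scores to placebo, so the remedy has to deal with that.

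**Conclusion.** The concern holds in limited form. The exit rules and the promise to analyse all randomised patients have not been reconciled. For removed patients, intention to treat would rest on partial data and untestable assumptions instead of observed end-of-period scores, and those removed in period 1 give no within-patient contrast.

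The size and net direction of any bias cannot be determined from the Protocol. The range of 1.8 to 1.6 against 2.0 rests on three assumptions: 10% to 20% stop amitriptyline, they gain nothing, and the opposing placebo route is ignored. It shows what could happen and is not an estimate. Loss of power is not the argument. The point merits correction because the change is small and the uncollected data cannot be recovered later.

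**What to change.** Reconcile the sections on side effects, withdrawal, ethics (rescue treatment) and both data and analysis sections. The clinical stopping and rescue rules stay as they are.

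1. Define stopping study drug and withdrawing from the study as separate events, with separate records.
2. Unless consent is withdrawn, continue the diary, calls and scheduled visits after drug is stopped, collect the planned end-of-period pain score, and analyse patients in their randomised sequence.
3. For anyone leaving altogether, record a pain score at exit, without delaying care.
4. State whether a patient who stops drug in period 1 is still assessed in period 2.
5. Flag scores taken after open amitriptyline, and report a sensitivity analysis that does not count them as placebo outcomes.

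The cost is protocol wording and continued follow-up of some patients using visits and calls that already exist. If a tenth of patients were affected, that would be about 12 of 124. The statistical downside is some dilution of the contrast from scores taken after a switch, which item 5 makes visible.

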### ***Follow up procedures: Day 4-day 15***

At home: one tablet will be taken at night for three nights. On the third day the study nurse will call to enquire as to adverse effects, pain score and any other problems, and advice on the next dosage. If the pain has abated significantly the dose will be left at one tablet at

night. If not, the dose will be increased to two tablets at night for three nights. The same procedure will occur until a maximum of 6 tablets at night has been reached. The participant will continue to take this dose for 4 weeks. A weekly telephone call will be conducted by the study nurse.

|                         |                                                                                                                                                                                                                                                                                                   |
|-------------------------|---------------------------------------------------------------------------------------------------------------------------------------------------------------------------------------------------------------------------------------------------------------------------------------------------|
| Day 3                   | The study nurse will call to enquire as to adverse effects, pain score and any other problems, and advice on the next dosage. If the pain has abated significantly the dose will be left at one tablet at night. If not, the dose will be increased by two tablets at night for three nights.     |
| Day 7                   | The study nurse will call to enquire as to adverse effects, pain score and any other problems, and advice on the next dosage. If the pain has abated significantly the dose will be left at two tablets at night. If not, the dose will be increased to three tablets at night for three nights.  |
| Day 11                  | The study nurse will call to enquire as to adverse effects, pain score and any other problems, and advice on the next dosage. If the pain has abated significantly the dose will be left at three tablets at night. If not, the dose will be increased to four tablets at night for three nights. |

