| Day 13                  | The study nurse will call to enquire as to adverse effects, pain score and any other problems, and advice on the next dosage. If pain has abated significantly the dose will be left at four tablets at night. If not the dose will be increased to six tablets at night. I                       |
| Week 3 day 15           | The study nurse will call to enquire as to adverse effects, pain score and any other problems, and advise to stay at the same dosage for the next 4 weeks                                                                                                                                         |
| Visit 3.0 Week 3 day 21 | Visit to study site. Check diary, questionnaire administered, medication check, discussion and information as required with participant, reimbursement, referral as required                                                                                                                      |
| Week 4 day 28           | The study nurse will call to enquire as to adverse effects, pain score and any other problems, and advise to stay at the same dosage for the next 3 weeks                                                                                                                                         |

|                         |                                                                                                                                                                                                                                                                                                                                                                                                                                                                                                             |
|-------------------------|-------------------------------------------------------------------------------------------------------------------------------------------------------------------------------------------------------------------------------------------------------------------------------------------------------------------------------------------------------------------------------------------------------------------------------------------------------------------------------------------------------------|

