| Visit 9.0 Week 9 day 63 | Visit to study site Check diary, questionnaire administered, medication check, discussion and information as required with participant, reimbursement, referral as required. Patient to receive new drug pack                                                                                                                                                                                                                                                                                               |
| Week 10 Day 66          | The study nurse will call to enquire as to adverse effects, pain score and any other problems, and advice on the next dosage. If the pain has abated significantly the dose will be left at one tablet at night. If not, the dose will be increased to two tablets at night for three nights.                                                                                                                                                                                                               |
| Day 69                  | The study nurse will call to enquire as to adverse effects, pain score and any other problems, and advice on the next dosage. If the pain has abated significantly the dose will be left at two tablet at night. If not, the dose will be increased to three tablets at night for three nights.                                                                                                                                                                                                             |

|                                                                   |                                                                                                                                                                                                                                                                                                                                                                                                                                                            |

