|-------------------------------------------------------------------|------------------------------------------------------------------------------------------------------------------------------------------------------------------------------------------------------------------------------------------------------------------------------------------------------------------------------------------------------------------------------------------------------------------------------------------------------------|
| Week 11 day 72                                                    | The study nurse will call to enquire as to adverse effects, pain score and any other problems, and advice on the next dosage. If the pain has abated significantly the dose will be left at three tablets at night. If not, the dose will be increased to four tablets at night for three nights.                                                                                                                                                          |
| Day 75                                                            | The study nurse will call to enquire as to adverse effects, pain score and any other problems, If not, the dose will be increased to six tablets at night.                                                                                                                                                                                                                                                                                                 |
| Day 78                                                            | The study nurse will call to enquire as to adverse effects, pain score and any other problems, and advice to stay on the same dosage for the next 4 weeks.                                                                                                                                                                                                                                                                                                 |

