| Visit 12.0 Week 12 day 82                                         | 
5. Visit to study site Check diary, questionnaire administered, medication check, discussion and information as required with participant, reimbursement, referral as required Collection of demographic data(Appendix I)
 
6. Collection of clinical data(Appendix II)
 
7. Assessment of peripheral neuropathy and other symptoms(Appendix III); if present refer to Palliative care
 
8. Assessment of coexisting pain medication
 |
| Day 91                                                            | The study nurse will call to enquire as to adverse effects, pain score and any other problems, and advice to stay on the same dosage for the next 2 weeks                                                                                                                                                                                                                                                                                                  |
| Day 98                                                            | The study nurse will call to enquire as to adverse effects, pain score and any other problems, and advice to stay on the same dosage for the next 1 weeks                                                                                                                                                                                                                                                                                                  |
| Exit procedure Week 15 is the exit visit and visit to study site. | Check diary, questionnaire administered, medication check, pain intensity score, clinical examination and discussion and information as required with participant, reimbursement, referral as required. Information on study results feedback session                                                                                                                                                                                                      |

[figure not shown]

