### **Guidelines for introducing amitriptyline**

Patients in this group will be given amitriptyline according to the following protocol. The dose of the drug will not be affected by the weight of the patient.

| Dose                                                                 | Days   |
|----------------------------------------------------------------------|--------|
| 25mg od at night
increase the dose on next visit if pain persists | Day 0  |
| 50mg od at night
increase the dose on next visit if pain persist  | Day 3  |
| 75mg od at night
increase the dose on next visit if pain persist  | Day 7  |
| 100mg od at night                                                    | day 11 |
| 150 mg od at night                                                   | Day 15 |

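### The protocol provides no step down from 150 mg: as written, a participant who cannot tolerate that dose either stays on it or stops and leaves the study

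*Protocol*

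**What the plan says.** **Titration.** Under Follow up procedures the dose climbs through one, two, three, four and six tablets (25 to 150 mg). At each titration call the nurse asks about adverse effects and pain, but the rule written for the next dose concerns pain: hold if it has eased enough, otherwise raise. The day 11 row reads "If not, the dose will be increased to four tablets at night for three nights" and the day 13 row "If not the dose will be increased to six tablets at night". Period 2 repeats the pattern, for example "If the pain has abated significantly the dose will be left at two tablet at night" on day 69. On day 75 the pain condition has fallen out of the sentence: "pain score and any other problems, If not, the dose will be increased to six tablets at night".

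**After titration.** The calls hold the dose: "advise to stay at the same dosage for the next 4 weeks" on day 15, "advice to stay on the same dosage for the next 2 weeks" on day 91.

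**Dose table.** Guidelines for introducing amitriptyline gives the same ladder. A persisting-pain condition stands against the first three doses, and the table ends at "150 mg od at night".

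**Response to side effects.** The Side effects section has a doctor assess anyone who develops them. It then offers three actions: raise the dose and continue, maintain it and continue, or "Stop the drug because of adverse events, and drop from the study".

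**What depends on this.** The primary objective in the Study Summary needs pain intensity at the start and end of each six-week period. Maximum tolerated dose is among the secondary outcomes. Both data analysis sections call for intention to treat, and the first specifies that everyone randomised is included.

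**The concern.** The ladder has a way up, a way to hold and a way out, but no way back. The gap matters most at the top. The last step is the largest (150 - 100 = 50 mg, against 25 mg for each earlier one). It also passes the 100 mg a day up to which the two earlier trials are cited as showing good tolerability (Clinical issues of importance when considering drug of choice).

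Three things are at stake. First, exits for intolerance at 150 mg would be expected mainly on amitriptyline, so end-of-period scores would go missing in relation to treatment. Second, the way out ends participation rather than just study drug, so the protocol itself creates gaps that an analysis of all randomised participants must then fill. Third, a participant who wants to remain in the trial has no written alternative to a dose tolerated badly.

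**Working it through.** No figure in the protocol is in dispute, so the check sets the dosing rules side by side.

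1. **Titration calls.** Days 3, 7, 11 and 13, then 66, 69, 72 and 75: 4 + 4 = 8. All ask about adverse effects. Seven state the pain condition (day 75 does not). None states what an adverse effect does to the dose. This counts wording only.

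2. **Later on-treatment calls.** Days 15, 28, 35, 78, 91 and 98: 6. All six advise the same dosage.

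3. **Listed actions by situation.**

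| Adverse effect arises at | Increase | Maintain | Stop |
|---|---|---|---|
| 100 mg or lower | possible, not sensible | holds the current dose; participant continues | participant leaves |
| 150 mg | not available (maximum) | holds 150 mg | participant leaves |

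In the first row, maintain is a usable answer. In the second, the only choices are to hold the dose that is not tolerated or to leave.

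4. **Time at the top dose.** A participant who reaches six tablets is asked to hold them for 42 - 13 = 29 nights by the period 1 call table, 42 - 15 = 27 by the dose table, or 105 - 75 = 30 in period 2 (week 15 is day 105). That is 27 to 30 of 42 nights.

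5. **What leaving costs.** Each participant should supply four primary scores: start and end of period 1, start and end of period 2.

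| Exit at 150 mg in | Scores obtained | Period changes obtained |
|---|---|---|
| Period 1 | 1 of 4 | 0 of 2 |
| Period 2 | 3 of 4 | 1 of 2 |

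Either way the within-person comparison that motivates the crossover is incomplete. Diary and telephone scores up to the exit remain, as does the mid-period visit if already made.

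6. **Maximum tolerated dose.** For someone who fails at 150 mg, the evidence that 100 mg was tolerated is the short stay there on the way up. A return to 100 mg, which would confirm it, is not provided.

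7. **Power.** If the 46 under Sample size calculations is read as the number needed in each ARV group, the margin is 62 - 46 = 16, and 16/62 = 26%. Moderate losses are covered on that reading, so the issue is which scores go missing rather than how many.

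**The case against.** The strongest reply is that the protocol does not ignore tolerability. Every call asks about adverse effects, and seven of the eight titration calls go straight on to advice about the next dose. A doctor assesses side effects, and extra visits for adverse events are allowed. The analysis restricted to those who reach the maximum dose expects participants with side effects to be excluded from it, which suggests that some were meant to stop short of 150 mg. This stands. A reader might infer from the pain-only wording that the dose must be raised whatever the side effects; the maintain option shows otherwise. None of these provisions, however, gives a way down once 150 mg has been taken.

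A reader might also infer that dose reduction is prohibited. It is not: the protocol omits it, and no sentence forbids it. Still, the list is framed as the set of available responses. An unlisted reduction during the fixed-dose weeks would depart from written procedure, and the Protocol violations section requires departures to be reported to the ethics committee and the DSMB within two days.

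The Side effects section also looks partly carried over from another design, since it gives a total study period of six weeks. That is fair, but it is current text. If the list is set aside, the crossover call tables contain no action at all for intolerance at 150 mg.

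Finally, the operating procedures and Appendix IV are not shown and may hold more detail. That cannot be excluded, although the procedures are to be based on the approved protocol, which contains no step down.

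**Conclusion.** The point holds as an omission with a consequence. Followed as written, the protocol leaves someone who tolerates 100 mg but not 150 mg a choice between holding 150 mg and leaving. Leaving forfeits the end-of-period score, and period 2 as well if it happens in period 1. This conflicts with the intention-to-treat aim and weakens the maximum tolerated dose outcome.

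The size cannot be estimated. The protocol gives no intolerance rate, so neither a number of exits nor a bias can be stated. That exits would fall more on amitriptyline is a reasonable expectation, not a figure from the document. A reader might infer that the primary result will be materially biased or the trial underpowered; the document supports neither.

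The slow elimination of nortriptyline, the varying number of nights at four tablets across the dosing tables, and the 25-75 mg range in the Placebo section are separate matters on which this conclusion does not rest.

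The change is worth making because it is inexpensive and protects participants, the primary endpoint and a named secondary outcome.

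**What to change.** 1. In the Side effects section, separate stopping drug from leaving the study. Replace the third action with: stop study drug, continue scheduled pain scores, and offer period 2 after washout if safe.
2. Add a fourth action to the same list: a blinded return to the last tolerated tablet count, identical in both periods, with that count recorded as the maximum tolerated dose.
3. In both call tables and the dose table, make each increase, above all from four to six tablets, conditional on pain not having eased enough and on no dose-limiting adverse effect; otherwise hold. Restore the missing condition on day 75.

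The cost is a protocol amendment and a revised dosing procedure. No new visits are needed, because scores after stopping use calls and visits already scheduled. No new supply is needed, because 150 mg is six 25 mg tablets and a lower count comes from the same pack. The drawbacks are a slightly lower mean active dose and a clinical judgement in titration, made blind. Whether 150 mg is the right ceiling is for the clinical team.
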